## Abstract

**Background:**

Bipolar disorders affect between 3–5% of the population and are associated with considerable lifelong impairment. Since much of the morbidity associated with bipolar disorder is caused by recurrent depressive symptoms, which are often only poorly responsive to antidepressants, there is a need to develop alternative, non-pharmacological interventions. Psychoeducational interventions have emerged as promising long-term therapeutic options for bipolar disorder.

**Methods/design:**

The study is an exploratory, individually randomised controlled trial. The intervention known as 'Beating Bipolar' is a psychoeducational programme which is delivered via a novel web-based system. We will recruit 100 patients with a diagnosis of DSM-IV bipolar disorder (including type I and type II) currently in clinical remission. The primary outcome is quality of life. This will be compared for those patients who have participated in the psychoeducational programme with those who received treatment as usual. Quality of life will be assessed immediately following the intervention as well as 10 months after randomisation. Secondary outcomes include current depressive and manic symptoms, number of episodes of depression and mania/hypomania experienced during the follow-up period, global functioning, functional impairment and insight. An assessment of costs and a process evaluation will also be conducted which will explore the feasibility and acceptability of the intervention as well as potential barriers to effectiveness.

**Discussion:**

Bipolar disorder is common, under-recognised and often poorly managed. It is a chronic, life-long, relapsing condition which has an enormous impact on the individual and the economy. This trial will be the first to explore the effectiveness of a novel web-based psychoeducational intervention for patients with bipolar disorder which has potential to be easily rolled out to patients.

**Trial registration:**

Current Controlled Trials ISRCTN81375447

## Background

Bipolar disorder is a severe recurrent disorder of mood and behaviour characterised by episodes of depression and mania or hypomania[1]. A clinical spectrum of bipolar disorder affects between 3–5% of the population and results in considerable lifelong social and occupational impairment [2-4]. Most of the morbidity associated with this disorder is caused by recurrent depressive episodes and chronic, low-grade depressive symptoms, which are present in most patients for at least half of their life-time[5,6].

There is currently considerable uncertainty about how best to treat these chronic depressive symptoms which have an enormous impact on the quality of life and functioning of large numbers of bipolar patients [7]. Much of this uncertainty concerns the use of antidepressants. Several studies suggest that a significant proportion of patients (between 30–50%) will respond poorly to antidepressants and may develop a chronic, cycling course of illness with more frequent depressive episodes, more suicidal behaviour and, in the longer-term, more treatment-resistance [8,9]. As a result, there is an urgent need to develop alternative, non-pharmacological interventions which might help to address chronic depressive features of the illness, as well as preventing manic relapses in the longer-term. Some studies of cognitive behavioural therapy for bipolar disorder have been positive [10-12]. However, a recent large randomised controlled trial found that benefit was limited to a small sub-group of patients [13]. Psychoeducational interventions, which tend to employ some cognitive-behavioural techniques in the context of adjunctive pharmacological management, have emerged as more promising long-term therapeutic options for bipolar disorder [14-18].

Most of the bipolar psychoeducation research to date has focused on group interventions [16-19]. Colom and Vieta have pioneered group psychoeducational interventions for bipolar disorder and have demonstrated that these programmes are effective in preventing relapse, are economically viable and are highly acceptable to patients [16,17,19]. A potential disadvantage of group psychoeducation is the considerable cost in terms of therapist time. As a result, group psychoeducation for bipolar disorder is not routinely available within the National Health Service (NHS). In order to make bipolar psychoeducational material more easily available to patients we have developed a novel, interactive, web-based, psychoeducational package for bipolar disorder which draws heavily on the positive aspects of the Barcelona model [16] and which has been produced in close consultation with patients, their families, carers and health professionals .

To our knowledge, there are no published data on the effectiveness of interactive or web-based psychoeducational programmes for bipolar disorder. The aim of the study is to assess a novel interactive psychoeducational intervention for bipolar disorder within an exploratory randomised controlled trial. The primary objective will be to assess whether those participating in the "Beating Bipolar" programme have improved quality of life compared to those in the control group. Secondary objectives include assessing whether those participating in the Beating Bipolar programme have improved scores on functioning, insight and depressive and manic symptoms and episodes. An assessment of costs and a detailed process evaluation exploring barriers, feasibility and acceptability of the intervention will also be completed. This paper describes the design of the trial.

## Methods/design

This is an exploratory (phase II) individually randomised controlled trial.

### The intervention: "Beating Bipolar"

The intervention was developed using an iterative process involving focus groups with patients, their carers and families and health professionals. The purpose of these groups was to advise on the design and content of the programme, as well as to revise and refine the intervention. Final decisions on the content were made by the research team. This process took 7 months. The primary focus of the intervention is the recognition and self-management of chronic depressive symptoms, depressive relapse and associated functional impairments. The intervention involves a blending of different delivery mechanisms, with initial face-to-face delivery, followed by written and web-based interactive delivery of factual content and ongoing support via a web forum. The web-based content requires the reader to be engaged in a number of interactive exercises in order to maximise long-term retention of the material.

The key areas covered in the package are: i) the accurate diagnosis of bipolar disorder; ii) the causes of bipolar disorder; iii) the role of medication; iv) the role of lifestyle changes; v) relapse prevention and early intervention; vi) psychological approaches; vii) gender-specific considerations and viii) advice for family and carers. The 8 modules are delivered online on a fortnightly basis over a four-month period. In order to maintain engagement, the modules are relatively brief at 20–30 minutes per module. There is an initial face-to-face introductory meeting with participants designed to engage them with the programme as well as to illustrate its use. Thereafter, participants will log onto the website and complete a module. Each module is then discussed within an online forum for participants, which will be moderated by a consultant psychiatrist ([name]). This forum will facilitate peer support and will allow us to provide clarification of module content, answer questions from participants and provide on-going support and engagement. The online forum will also be important in terms of assessing the acceptability of the intervention.

### Outcome measures

The primary outcome measure is the World Health Organisation Quality of Life assessment tool, Brief version (WHOQOL-Bref) [20] (see Table 1). This provides an assessment of overall quality of life. It is comprised of scores within four separate domains (physical health, psychological health, social relationships and environment). It is a reliable, valid and widely-used measure of quality of life in psychiatric out-patient settings [21]. A review concluded that there is currently no quality of life measure for specific use in bipolar patients, however the WHO-QOL is recommended for this population [22].

**Table 1 T1:** Outcome Measures and Assessments

	Baseline assessment	Interim assessment (at end of treatment)	Final assessment (6 mth after treatment)
	By interview at t = 0 months	By post at t = 4 months	By interview at t = 10 months
**Primary Outcome:**			
WHOQOL-Bref	+	+	+

**Secondary Outcomes:**			

MINI assessment	+	---	+

MADRS	+	---	+

YMRS	+	---	+

GAF	+	---	+

FAST	+	---	+

SAI	+	---	+

Use of health service resources	---	---	+

Process measures:			
Interviews Use of software	---	---	+

WHOQOL-Bref: World Health Organisation Quality of Life Assessment, Brief Version; MINI: Mini International Neuropsychiatric Interview; MADRS: Montgomery Asberg Depression Rating Scale; YMRS: Young Mania Rating Scale; GAF: Global Assessment of Functioning Scale; FAST: Functioning Assessment Short Test; SAI: Schedule of Assessment of Insight

Secondary outcomes will examine functioning using the Global Assessment of Functioning (GAF) and Functioning Assessment Short Test (FAST) scales and insight, using the Schedule of Assessment of Insight (SAI). Current depressive symptoms according to the Montgomery Asberg Depression Rating Scale (MADRS) and current manic symptoms according to the Young Mania Rating Scale scale (YMRS), will also be compared between the two groups. Using the Mini International Neuropsychiatric Interview (MINI), the number and severity of depressive and manic symptoms and number and timing of episodes of depression and mania or hypomania experienced during the follow-up period will be compared between groups (this will permit assessments of time to relapse)

### Sample size

Based on our own work and the work of others using the WHOQOL-Bref in mood disordered patients, we expect that the mean score for patients at entry will be 65 (standard deviation 14.4) and that a meaningful clinical response will be a difference between experimental and control groups of 10 or more points [23]. For an 80% chance of detecting this difference on the WHOQOL-Bref, at a significance level of 0.05, 32 patients are needed in each arm of the trial at follow-up. We will recruit 50 patients into each arm of the study which, allowing for a 30% attrition rate, will mean that 35 patients in each arm will complete the trial. Our recruitment strategy and our extensive contacts with local clinical services and patient groups mean that this target of 100 patients recruited into the trial is realistic and achievable.

### Recruitment

Participants will be identified and recruited from multiple sources across South Wales, including Cardiff Primary Care Practices, Cardiff Community Mental Health Teams (CMHTs) and local branches of the Manic Depression Fellowship. Our recruitment strategy will be aided by using the resources of the Mental Health Research Network for Wales (MHRN-Cymru) and the Primary Care Mental Health Research Network in Wales (PCMHRN-Cymru).

### Inclusion criteria

The main inclusion criterion for this study will be a diagnosis of DSM-IV bipolar disorder (including type I and type II) currently in clinical remission. Clinical remission has been chosen as an inclusion criterion because this is an exploratory trial of an intervention which requires participants to be able to fully engage with psychoeducational material. It is also the case that the primary outcome is a measure of quality of life rather than clinical symptoms. Diagnosis will be assessed using the Mini International Neuropsychiatric Interview (MINI) [24] and clinical remission will be defined as not fulfilling diagnostic criteria for a depressive, manic or mixed affective episode during the preceding 3 month period, plus a current Montgomery Asberg Depression Rating Scale (MADRS) score of less than or equal to 10 [25,26] and a Young Mania Rating Scale score of less than or equal to 8 [27]. These MADRS and YMRS threshold scores are widely accepted correlates of symptomatic remission in bipolar disorder. Participants must also be aged between 18 and 65 for inclusion in this study.

### Exclusion criteria

These will include an inability to engage fully in the psychoeducational programme (for example, because of cognitive impairment or not having English language of a sufficient level), not meeting diagnostic criteria for bipolar disorder, and not being in clinical remission according to the definitions above. Given that this is an exploratory trial, no other exclusion criteria will be specified.

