**Figure 1 F1:**
[figure not shown]
**BIPED Trial Design**.

Delivery of the intervention will begin within 2 weeks of randomisation. Both arms of the study will receive TAU, which will be ongoing care by CMHTs and/or General Practitioners (GPs). We will attempt to minimise potential contamination between groups by giving those in the experimental group individual logins to the website and emphasising the importance of keeping these details private. We will also monitor use of the software and explore possible contamination during the process evaluation interviews. In order to minimise demoralisation and drop-out in the control arm, all participants will be offered the intervention at the end of the follow-up period if the intervention appears to be effective. The intervention will last for 4 months. There will be an interim assessment at the end of the intervention, which will be a postal questionnaire of the WHOQOL-Bref. The primary outcome point will be 10 months from randomisation and all measures will be reassessed at this point (Figure 1 and Table 1).

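### The closed exclusion list lets patients who helped shape the package in its development focus groups be randomised, and the contamination safeguards do not cover exposure before entry

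*Protocol article*

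**What the plan says.** All references are to the protocol article.

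- **The intervention: Beating Bipolar.** "The intervention was developed using an iterative process involving focus groups with patients, their carers and families and health professionals". On what the groups did: "The purpose of these groups was to advise on the design and content of the programme, as well as to revise and refine the intervention". On duration: "This process took 7 months". The research team took the final decisions on content.
- **Inclusion criteria.** A DSM-IV bipolar diagnosis (type I or II), clinical remission by the stated definition, and age 18 to 65.
- **Exclusion criteria.** Inability to engage (for example, because of cognition or language), no bipolar diagnosis, or no remission. The list then ends: "Given that this is an exploratory trial, no other exclusion criteria will be specified".
- **Recruitment.** "Participants will be identified and recruited from multiple sources across South Wales", including local branches of a patient organisation.
- **Trial procedures (text after Figure 1).** Contamination is to be limited by "giving those in the experimental group individual logins to the website and emphasising the importance of keeping these details private". In addition: "We will also monitor use of the software and explore possible contamination during the process evaluation interviews".
- **Process evaluation.** The interviews are with around 20 participants, all from the intervention group, chosen to vary in sex, age and level of engagement.

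**The concern.** The trial compares people who receive the package with people who do not. A patient who spent part of the development period discussing and improving its content has already met some of what treatment as usual is meant to lack. Randomised to control, that patient is a partly exposed control. Randomised to the intervention, the same patient may have less left to gain. Either way, the contrast would be expected to narrow.

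The feasibility side is also affected. Acceptability and engagement findings are meant to inform a phase III trial, and someone who helped to design a programme is not a neutral judge of it. Nothing in the interview sampling keeps such people out.

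The article plainly regards contamination as a threat, but every safeguard it names looks at what happens after randomisation. This is not a detail lost when a full protocol was condensed into an article, because the article itself says that no further exclusion will be set.

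**Working it through.** **Step 1. Does the text admit these patients?** Take a focus-group patient aged 18 to 65, in remission and able to engage, and run through the rules.

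| Rule | Result |
|---|---|
| Bipolar diagnosis, remission, age 18 to 65 | met |
| Unable to engage | does not apply |
| No bipolar diagnosis, or not in remission | does not apply |
| Any other exclusion | none, by the closing sentence |

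The patient is eligible.

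**Step 2. Would a safeguard catch a pre-exposed control?** Private logins restrict access to the website by people outside the intervention arm. Software monitoring records use during the trial. The contamination interviews are held only in the intervention arm. None of these would identify a control who met the content before entry.

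**Step 3. Reproduce the planned sample size.** Inputs from the Sample size section: difference 10, SD 14.4, power 80%, significance level 0.05 (sidedness not stated; two-sided assumed, since a one-sided test would need only 26 per arm).

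n per arm = 2 × [14.4 × (1.960 + 0.842) / 10]² = 32.55, or 33 rounded up. The article's 32 agrees to within one patient. Completers: 50 × (1 − 0.30) = 35 per arm, as stated.

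**Step 4. Power with no pre-exposure.** The standard error of the difference at 35 per arm is 14.4 × √(2/35) = 3.442. Then 10 / 3.442 = 2.905, and power = Φ(2.905 − 1.960) = 0.828 (0.817 with the t distribution).

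**Step 5. Power with pre-exposure.** Let f be the share of each arm that is pre-exposed and g the share of the effect lost in those patients. The expected difference is 10 × (1 − f × g). The article gives neither f nor g, so both are assumptions. Power is by the normal approximation at 35 per arm.

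| f | g = 1: difference | g = 1: power | g = 0.5: difference | g = 0.5: power |
|---|---|---|---|---|
| 0 | 10 | 0.828 | 10 | 0.828 |
| 2% | 9.8 | 0.812 | 9.9 | 0.820 |
| 4% | 9.6 | 0.796 | 9.8 | 0.812 |
| 10% | 9.0 | 0.744 | 9.5 | 0.788 |

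Worked line for f = 4%, g = 1: 9.6 / 3.442 = 2.789, and Φ(2.789 − 1.960) = 0.796. Total loss of effect is the worst case on the dilution side.

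**Step 6. Interviews.** If interviewees reflected the arm, 4% pre-exposed would mean 20 × 0.04 = 0.8 of about 20, or roughly one person.

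**The case against.** The strongest reply is that this is a gap on paper only. The article does not say how many patients sat in the groups, where they came from, or that any will be invited. Its remark about "our extensive contacts with local clinical services and patient groups" explains why the recruitment target is achievable and says nothing about the focus groups. That stands: regional recruitment makes overlap plausible but does not show it.

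Second, advising on content is not the same as receiving the programme. The intervention is an introductory meeting, eight interactive modules over four months and a moderated forum. A co-designer in the control arm would still lack these, so total loss of effect is unlikely. Keener engagement by co-designers in the intervention arm could also push the difference the other way. Both points stand, and they make the g = 1 column an upper limit on dilution rather than a forecast.

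Third, randomisation balances prior exposure on average, and the primary ANCOVA adjusts for baseline WHOQOL-Bref. This stands against any charge of confounding. It does not restore the contrast: adjustment accounts for a gain already present at entry but does not make an exposed control unexposed.

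Fourth, the article gives a reason for few exclusions, namely that the trial is exploratory. That explains a broad clinical entry rule. It is not a reason to admit people who have already seen the material.

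**Conclusion.** The point holds as a gap in eligibility that is cheap to close. As written, focus-group patients can be randomised to either arm, and the contamination measures do not address what they met before entry.

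If some do enrol, the likely effect is a modest loss of contrast. With 4% of each arm pre-exposed and no effect in them, 10 points become 9.6 and power goes from 0.828 to 0.796. With half the effect retained, power is 0.812. These figures rest on assumed values of f and g, an equal share in each arm, SD 14.4 and a two-sided 0.05 test. The acceptability interviews could also be less neutral, whatever the size of the dilution.

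A reader might infer more, and the article does not support it:

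- **That the comparison is diluted.** No overlap is documented, and the direction is likely rather than certain.
- **That the comparison is biased by confounding.** Random allocation protects against that on average.
- **That co-designers would form a sizeable part of the interview sample.** At the shares considered likely to matter here, proportional sampling gives about one in 20, and the sampling deliberately spans levels of engagement.

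**What to change.** Add one exclusion to the Exclusion criteria section: patients who themselves took part in the focus groups that developed the package. Check it by asking each candidate at screening, since the article does not say whether an attendance record exists. The exclusion need not extend to patients whose relatives or carers attended, because nothing in the article shows that those patients saw the material. Nor does it need to cover pilot testers, because the article mentions no pilot testing by patients.

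If any focus-group patients have already been randomised, keep them in the intention-to-treat analysis, flag them, report a sensitivity analysis without them, and do not select them for the acceptability interviews.

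The cost is one sentence, one screening question and the loss of a small but unknown number of candidates. The sample size calculation does not change.

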### Trial procedures: consent, baseline assessments and randomisation

All potential participants will receive an invitation letter and a detailed information sheet about the study inviting them to approach the research team if they are interested in taking part. They will be asked to provide written consent before being screened for the inclusion and exclusion criteria using the MINI interview and MADRS/YMRS assessments (see Figure 1). Participants identified as eligible will also complete the WHOQOL-Bref [20], the GAF Scale [28], the FAST [29] and the SAI [30]. Participants will be individually randomised remotely using computer-generated number lists to either, the Beating Bipolar intervention plus treatment-as-usual (TAU) or TAU alone.

**Figure 1 F1:**
[figure not shown]
**BIPED Trial Design**.

Delivery of the intervention will begin within 2 weeks of randomisation. Both arms of the study will receive TAU, which will be ongoing care by CMHTs and/or General Practitioners (GPs). We will attempt to minimise potential contamination between groups by giving those in the experimental group individual logins to the website and emphasising the importance of keeping these details private. We will also monitor use of the software and explore possible contamination during the process evaluation interviews. In order to minimise demoralisation and drop-out in the control arm, all participants will be offered the intervention at the end of the follow-up period if the intervention appears to be effective. The intervention will last for 4 months. There will be an interim assessment at the end of the intervention, which will be a postal questionnaire of the WHOQOL-Bref. The primary outcome point will be 10 months from randomisation and all measures will be reassessed at this point (Figure 1 and Table 1).

